## Abstract

**Background:**

COPD is a progressive lung disorder with rates of mortality between 36–50%, within 2 years after admission for an acute exacerbation. While treatment with inhaled bronchodilators and steroids may partially relieve symptoms and oxygen therapy may prolong life, for many patients the course of the disease is one of inexorable decline. Very few palliative care intervention studies are available for this population. This trial seeks to determine the effectiveness of the introduction of specialized palliative care on hospital, intensive care unit and emergency admissions of patients with severe and very severe COPD.

**Methods/Design:**

The study is a three year single centre, randomized controlled trial using a 2 arms parallel groups design conducted in a tertiary center (University Hospitals; Geneva). For the intervention group, an early palliative care consultation is added to standard care; the control group benefits from standard care only. Patients with COPD defined according to GOLD criteria with a stage III or IV disease and/or long term treatment with domiciliary oxygen and/or home mechanical ventilation and/or one or more hospital admissions in the previous year for an acute exacerbation are eligible to participate. Allocation concealment is achieved using randomisation by sealed envelopes. Our sample size of 90 patients/group gives the study a 80% power to detect a 20% decrease in intensive care unit and emergency admissions – the primary endpoint. All data regarding participants will be analysed by a researcher blinded to treatment allocation, according to the "Intention to treat" principle.

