Most patients with a life-limiting illness prefer to discuss their preferences for end-of-life care relatively early in the course of their illness, as these discussions are less stressful when the patient is feeling relatively well
[31]. One qualitative study compared patients with severe COPD to patients with metastatic cancer or advanced AIDS, showed that patients with COPD were more likely to express concern about the lack of information that they received about their disease. They wanted more information in the following five specific areas: diagnosis and disease process, treatment, prognosis, what dying might be like, and advance care planning
[32].

A recent randomized study conducted in the United States in an outpatient clinic demonstrated that an intervention using patient specific feedback about preferences for discussing end-of-life care improved the occurrence and the quality of communication between 376 patients with COPD and their clinicians. Patients in the intervention group reported nearly a threefold higher rate of end-of-life discussions about end-of-life care (30% vs. 11%; P < 0.01)
[33].

Advance directives may be especially useful among patients with COPD because of their likely trajectory of illness, with unpredictable exacerbations that may render patients suddenly critically ill. Some patients with COPD have strong feelings about the situations in which they would want to forego CPR or, particularly relevant for COPD, mechanical ventilation for acute respiratory failure. Patients’ prior experiences with life support, or with relatives or friends who have required life support, can be important facilitators for patient–physician communication about treatment preferences and end-of-life care
[34]. The period of hospitalization may not be an appropriate time to initiate advance directives, but the opportunity should be taken after discharge from hospital
[35].

Because of the paucity of palliative care intervention studies available for this particular population, we designed a study to evaluate the effect of introducing palliative care for patients with severe and very severe COPD.

Our hypothesis is that the early introduction of specialized palliative care could decrease the length and number of admissions to intensive care units as well as hospital and emergency admissions of patients with severe and very severe COPD.

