The primary objective of the study is to assess the effectiveness of the introduction of early specialized palliative care on hospital, intensive care unit and emergency admissions of patients with severe and very severe COPD.

The secondary objectives are to assess impact of early palliative care on:

1. mood and anxiety of patients with severe and very severe COPD

2. health-related quality of life of patients with severe and very severe COPD.

3. pattern of antibiotics used during the last month of life

4. advance care planning and end-of-life decision-making

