### Outcomes measures

Regarding the primary outcome, Hospital, ICU and emergency admissions will be collected in both groups form the medical records once a month. Length of stay in the different divisions, type of divisions (i.e.: internal medicine, rehabilitation) and reasons for admissions will be collected.

Regarding the secondary outcomes of the study:

– Mood and anxiety of patients will be measured with the self-assessment instrument: the Hospital Anxiety and Depression Scale (HADS)
[50,51]

– Quality of life will be measured with the SF-36 short form: a self-assessment scale validated in this population, and the COPD Assessment Test (CAT): a short, simple instrument for quantifying the symptom burden of COPD in routine practice

– Use of antibiotics during the last three months will be recorded

– Completion of advance directives, documented preferences for resuscitation, or nomination of surrogate decision maker will also be recorded

The secondary outcomes will be collected at baseline and at weeks 12, 24, 36 and 48.

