### Power calculation

One hundred-thirteen patients are currently followed by the Division of Pulmonary Disease in the University Hospital Geneva because of treatment with NIV and/or LTOT. We know that between one third and one half of these patients are hospitalized at least once during the year. Furthermore approximately 200 COPD patients per year are admitted to the Emergency Division of our hospital. Even if only a third of these patients are included in the study, this would give us sufficient statistical power to validly analyze our primary outcomes. Regarding the primary outcome, we calculated that a sample size of 80 patients per group would be adequate with an 80% power to detect a difference in hospital admissions of 20% between both groups at an α significance level (2-sided test) of 0.05.

With regard to missing data, we will use the conservative approach of carrying the last observation forward for all missing data in the intention-to-treat analyses. Poisson or binomial negative regression models will be used to compare count data between the groups while adjusting for potential confounder. The trend in the evolution of the different scores will be assessed using mixed linear regression models.

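### The article contradicts itself on the primary endpoint: three incompatible versions, two of them with different sample sizes, so the success criterion cannot be identified

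*Protocol article*

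**What the plan says.** The article describes the primary endpoint in these places:

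- **Abstract, Methods/Design:** 90 per group is said to give 80% power for a "20% decrease in intensive care unit and emergency admissions – the primary endpoint". Hospital admissions are not mentioned.
- **Power calculation:** for the primary outcome, 80 per group is said to be adequate "with an 80% power to detect a difference in hospital admissions of 20% between both groups", at a two-sided 0.05. ICU and emergency admissions are not mentioned. The same paragraph also uses the plural for primary outcomes.
- **Primary objective (end of Background):** "effectiveness of the introduction of early specialized palliative care on hospital, intensive care unit and emergency admissions".
- **Outcomes measures:** "Regarding the primary outcome, Hospital, ICU and emergency admissions will be collected in both groups". The next sentence adds "Length of stay in the different divisions, type of divisions" and reasons for admission as items to be collected.

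The study hypothesis, also at the end of Background, expects the intervention to "decrease the length and number of admissions to intensive care units as well as hospital and emergency admissions". It does not call any of these the primary endpoint.

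**The concern.** The abstract and the Power calculation section each claim 80% power for the primary endpoint, yet they name endpoints with no admission type in common and give different sample sizes. The objective and the Outcomes measures section give a third, wider version. These are conflicting statements about what the trial is designed to show, which is different from detail left out for brevity.

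Two things are at stake. First, the success criterion is not fixed: an effect on hospital admissions alone, on ICU and emergency admissions alone, or on some combination could each be presented as the primary result. Second, the stated power can be judged only against a defined endpoint with a control rate, and the abstract's endpoint has no such rate in the document.

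**Working it through.** **1. The versions side by side**

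| Place | Primary endpoint | Per group | Power |
|---|---|---|---|
| Abstract, Methods/Design | ICU and emergency admissions | 90 | 80% |
| Power calculation | Hospital admissions | 80 | 80% |
| Primary objective; Outcomes measures | Hospital, ICU and emergency admissions | not given | not given |

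The first two rows share no admission type. The third does not say composite or separate. Length of stay is collected under the primary-outcome paragraph with no stated status.

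**2. Reproducing the 80 per group**

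Inputs from the document: 1:1 allocation (Randomisation-allocation concealment); two-sided 0.05, 80% power and a 20% difference (Power calculation). The only annual per-patient rate is that one third to one half of the patients followed for NIV and/or LTOT are hospitalised at least once a year (Power calculation). The document does not say that this rate was used, or whether 20% is absolute or relative.

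Formula for two proportions, with p̄ the mean of p1 and p2:

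n = [1.96·√(2p̄(1−p̄)) + 0.842·√(p1(1−p1) + p2(1−p2))]² / (p1−p2)²

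*Absolute 20-point drop:*

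- p1 = 1/3, p2 = 0.133: (1.172 + 0.489)² / 0.04 = 69.01, so 70.
- p1 = 0.39, p2 = 0.19: (1.258 + 0.527)² / 0.04 = 79.6, so **80**.
- p1 = 0.50, p2 = 0.30: (1.358 + 0.571)² / 0.04 = 93.0, so 93.

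With a continuity correction the range is 79 to 103. The abstract's 90 also falls within these ranges (90 at p1 = 0.39 with correction; 89 at p1 = 0.45 without). It would equally fit 80 inflated for about 11% attrition, since 80/0.89 = 89.9. The document states neither derivation.

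*Relative 20% reduction:*

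- p1 = 1/3, p2 = 0.267: 741 per group; power with 80 per group is 15%.
- p1 = 0.50, p2 = 0.40: 388 per group; power with 80 per group is 24%.

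*Number of admissions, rate ratio 0.8, Poisson, mean μ per year in the control group (assumed):*

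n = (1.96 + 0.842)² · (1/μ + 1/(0.8μ)) / (ln 0.8)² = 7.849 × 2.25 / 0.0498 / μ ≈ 355/μ

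- μ = 1: about 355 per group.
- μ = 2: about 178 per group.
- To reach 80 per group, μ would have to be about 355/80 = 4.4 admissions a year. No such rate is given. Overdispersion raises n further.

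Of the readings tried, only the absolute drop in the proportion admitted gives about 80 per group from a rate that the document states.

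**3. The abstract's endpoint**

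No per-patient rate of ICU or emergency admission is given. The roughly 200 COPD patients a year seen in the Emergency Division are a count without a denominator. The abstract's power claim therefore cannot be checked on its own inputs.

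**4. Error rate if the three types were tested separately**

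Assumption: three two-sided tests, each at 0.05, equally correlated.

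- Independent: 1 − 0.95³ = 14.3%.
- Correlation 0.5: 12.5%.
- Correlation 0.9: about 8%.

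The correlations are assumed; no figure in the document fixes them. Closely linked admissions would put the value nearer the lower end.

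Splitting 0.05 equally over three tests (0.0167 each), with the absolute 20-point drop in each and control rates of 1/3 to 1/2 (assumed for all three), would need 93 to 125 per group. Power would be 79% to 64% with 90 per group and 73% to 58% with 80.

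**The case against.** The strongest defence is that the article is largely consistent. The abstract's background, the primary objective, Outcomes measures and Discussion all list hospital, ICU and emergency admissions, and only two sentences narrow the set. A condensed article may also leave the composite definition and any division of alpha to an analysis plan that is not shown. The second part stands: the absence of a multiplicity rule is not a finding here. The first does not remove the conflict, because the two sentences that narrow the set are the ones that carry the power claims, and they narrow it in different directions.

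Several stronger readings are tempting but not supported:

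- **A fourth version that includes length of stay.** The hypothesis is not labelled a primary endpoint, and length of stay is only listed as collected. Its status is unclear, no more.
- **Full alpha for every endpoint.** The only alpha stated is attached to hospital admissions. Separate testing at 0.05 would be inferred from silence.
- **A 14.3% error rate.** This is the ceiling under independence, and the three admission types are unlikely to be independent.
- **Lower power for ICU admissions.** This needs an ICU rate and an expected effect; neither is given.
- **One exacerbation counted up to three times.** An episode could pass through several units, but no section says that the three types are summed.

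**Conclusion.** The contradiction is established by the text alone and needs no assumption: three incompatible versions of the primary endpoint, two of them tied to different sample sizes at the same 80% power. The success criterion cannot be identified, and the abstract's power claim has no stated basis. This must be resolved.

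The numerical consequences are conditional. The match with 80 per group assumes an absolute 20-point drop in the proportion hospitalised and a control rate near 0.39, inside the stated range. The family-wise error of about 8% to 14% assumes separate tests at 0.05 and correlations from 0.9 down to zero. A reader might infer that the sponsor intends to choose among endpoints after seeing the data; the document does not show that.

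**What to change.** Before any between-group data are seen:

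1. Name one primary endpoint with its unit and time window. One option is the proportion of patients with at least one hospital admission within 12 months, the reading that gives about 80 per group. Another is a defined composite of the admission types, with each episode counted once.
2. Tie a single sample size and power statement to it, giving the control rate used, whether 20% is absolute or relative, and how 80 and 90 relate.
3. If a count is chosen, recalculate and restate the power, because 80 per group does not follow for a count (about 355 per group at rate ratio 0.8 and an assumed mean of 1 a year).
4. Make the remaining admission types and length of stay secondary, or place them in a stated hierarchy.
5. Align the abstract, the primary objective, Outcomes measures and Power calculation.

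The cost is more than wording. Recruitment started in September 2013 (Ethics approval), so the change needs a dated amendment. Results on the other admission types could no longer be claimed as primary, and the restated power may be less favourable.

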**Discussion:**

Given the trends toward aggressive and costly care near end-of-life among patients with COPD, a timely introduction of palliative care may limit unnecessary and burdensome personal and societal costs, and invasive approaches. The results of this study may provide directions for future palliative care interventions in this particular population.

**Trial registration:**

This trial has been registered at clinicaltrials.gov under
NCT02223780

## Background

Chronic obstructive pulmonary disease (COPD) is the fourth leading cause of mortality and the 12th leading disability worldwide
[1,2]. It is a progressive lung disorder with mortality rates between 36–50%, within 2 years after admission for an acute exacerbation
[3]. One out of eight (130,000) hospital admissions per year in the UK are related to COPD with approximately 30% of patients admitted with COPD for the first time being re-admitted within 3 months
[4].

While treatment with inhaled bronchodilators and steroids may partially relieve symptoms and Noninvasive Positive Pressure Ventilation (NIV) and long term oxygen therapy (LTOT) may prolong life, for many patients the course of the disease is one of inexorable decline with a prolonged period of disabling dyspnea and increasingly frequent hospital admissions reflecting deteriorating lung function and usually presaging a premature death
[5]. It has long been recognized that, in this group of patients, both quality of life and survival are poor. For instance, in the Nocturnal Oxygen Therapy trial of LTOT, disturbances in emotional and social functioning were common and there was a marked impairment in activities of daily living
[6].

Despite these issues, the needs of these patients are typically poorly addressed, and many patients have limited access to specialists in palliative care services
[7-10]. Furthermore many of these patients are housebound and they and their caregivers have poor access to health services. No randomised early palliative care intervention studies are available for this particular population, although it has been shown that it is feasible to provide palliative care interventions in this population
[11-15] A study conducted in the UK found that patients with COPD are much less likely to die at home and to receive palliative care services than patients with lung cancer
[7]. Additional studies have also documented the poor quality of palliative care and significant burden of symptoms among patients with COPD
[7,8,16-19]. In a retrospective cohort study conducted in Canada, of 1098 patients who died in 2004, very few patients who died with COPD used the palliative care services that were available in acute care hospitals (5.1%) or home care settings (2.8%) compared to those with lung cancer (acute care 47.6%; home care 37.4%)
[20].

Although anxiety and depression are common in COPD, they are not well recognized or treated
[21]. In a recent study, only a third of patients with COPD and clinically significant depression or anxiety were being treated and only half of those with severe depression or anxiety were being treated
[22]. Antidepressants can significantly improve mood among patients with COPD and depression
[23].

One reason these patients may receive poor-quality palliative care is that patient–physician communication about end-of-life care often occurs late in the illness
[24,25]. Healthcare for these patients is often initiated in response to acute exacerbations rather than being initiated proactively based on a previously developed plan for managing their disease
[26].

Studies have shown that only a minority of patients with moderate-to-severe COPD has discussed treatment preferences and end-of-life care issues with their physicians and most believe that their physicians do not know their preferences for end-of-life care
[24,25,27]. A survey of 214 general practitioners in the UK found that, although 82% felt that general practitioners should discuss prognosis with COPD patients, only 41% reported "often" or "always" discussing prognosis with these patients
[28]. Furthermore, two thirds of the physicians who reported infrequently discussing end-of-life care reported feeling inadequately prepared to have such discussions.

The "SUPPORT" study (study to understand prognosis and preferences for outcomes and treatment) that/which enrolled seriously ill hospitalized patients, including COPD, demonstrated that COPD compared to patients with lung cancer, were much more likely to die in the intensive care unit, on mechanical ventilation and with dyspnea
[29]. These differences occurred despite most patients with COPD preferred treatment focused on comfort rather than on prolonging life. In fact, SUPPORT found that patients with lung cancer and patients with COPD were equally likely to prefer not to be intubated and not to receive cardiopulmonary resuscitation (CPR), yet patients with COPD were much more likely to receive these therapies
[29]. A study of patients with COPD or lung cancer in the US Veterans Affairs Health System also found that patients with COPD were much more likely to be admitted to an ICU, and have greater lengths of stay in the ICU during their terminal hospitalization, than patients with lung cancer
[30].

Most patients with a life-limiting illness prefer to discuss their preferences for end-of-life care relatively early in the course of their illness, as these discussions are less stressful when the patient is feeling relatively well
[31]. One qualitative study compared patients with severe COPD to patients with metastatic cancer or advanced AIDS, showed that patients with COPD were more likely to express concern about the lack of information that they received about their disease. They wanted more information in the following five specific areas: diagnosis and disease process, treatment, prognosis, what dying might be like, and advance care planning
[32].

A recent randomized study conducted in the United States in an outpatient clinic demonstrated that an intervention using patient specific feedback about preferences for discussing end-of-life care improved the occurrence and the quality of communication between 376 patients with COPD and their clinicians. Patients in the intervention group reported nearly a threefold higher rate of end-of-life discussions about end-of-life care (30% vs. 11%; P < 0.01)
[33].

Advance directives may be especially useful among patients with COPD because of their likely trajectory of illness, with unpredictable exacerbations that may render patients suddenly critically ill. Some patients with COPD have strong feelings about the situations in which they would want to forego CPR or, particularly relevant for COPD, mechanical ventilation for acute respiratory failure. Patients’ prior experiences with life support, or with relatives or friends who have required life support, can be important facilitators for patient–physician communication about treatment preferences and end-of-life care
[34]. The period of hospitalization may not be an appropriate time to initiate advance directives, but the opportunity should be taken after discharge from hospital
[35].

Because of the paucity of palliative care intervention studies available for this particular population, we designed a study to evaluate the effect of introducing palliative care for patients with severe and very severe COPD.

Our hypothesis is that the early introduction of specialized palliative care could decrease the length and number of admissions to intensive care units as well as hospital and emergency admissions of patients with severe and very severe COPD.

The primary objective of the study is to assess the effectiveness of the introduction of early specialized palliative care on hospital, intensive care unit and emergency admissions of patients with severe and very severe COPD.

The secondary objectives are to assess impact of early palliative care on:

1. mood and anxiety of patients with severe and very severe COPD

2. health-related quality of life of patients with severe and very severe COPD.

3. pattern of antibiotics used during the last month of life

4. advance care planning and end-of-life decision-making

